XVR011 is a single domain (heavy chain only) antibody fragment (VHH) which is linked to the Fc part of a human immunoglobulin G subclass 1 (IgG1). The VHH component was derived from a heavy chain only antibody from a llama, which had been inoculated with SARS-CoV-1 spike protein. When SARS-CoV-2 was identified, the VHH was found to be cross reactive to its spike protein. The VHH binds to an epitope on the receptor-binding domain of the SARS-CoV-2 spike protein and through steric hindrance, blocks the interaction of the spike protein with the ACE2 receptor and thereby prevents the virus from entering the cell and replicating. The binding site is partially hidden and is expected to be less susceptible to genetic pressure and viral mutation. The amino acid sequence of the VHH was further humanized and optimized to increase its antiviral potency. In XVR011, two VHH's are linked to a human IgG1 crystallizable fragment (Fc) fragment with the aim of achieving a half-life similar to that of naturally occurring antibody, i.e. approx. 21 days. The Fc has been modified to partially silence the effector function. This has been done to minimise the potential for antibody-dependent disease enhancement. The XVR011-virus complex is expected to be cleared by non-specific mechanisms such as non-specific pinocytosis.

Rapid neutralisation of SARS-CoV-2 before the immune system has reached the point where an excessive inflammatory reaction has been triggered may potentially reduce the morbidity and mortality associated with COVID-19. The potential of XVR011 to achieve this is being evaluated in this Phase 1/2 clinical trial in patients with symptomatic COVID-19 who are hospitalised but in whom the inflammatory component does not yet require intensive care treatment or mechanical ventilation. The objective is to neutralise the virus more rapidly and achieve a more rapid recovery, reduction in the need for medical care as well as prevent the need for mechanical ventilation and/or intensive care.

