| Optional blood sample for future exploratory biomarker testing (central lab)                                              |                        | X (pre-dose)              |                                                                           | X              |                |              |               |                |                |              |              |                |                 |
| Pregnancy test (WOCBP only) f                                                                                  | X                      |                           |                                                                           |                |                |              |               |                | X              | X            | X            |                | X               |
| FSH (post-menopausal women only) g                                                                             | X                      |                           |                                                                           |                |                |              |               |                |                |              |              |                |                 |
| Anti-SARS-CoV-2 antibody test                                                                                             |                        | X (pre-dose)              |                                                                           |                |                |              |               |                |                |              |              |                |                 |
| Viral load nasopharyngeal sample                                                                                          |                        | X (pre-dose)              |                                                                           | X              |                | X            |               |                |                |              |              | X              |                 |

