| 
To evaluate the antiviral activity of a single intravenous XVR011 infusion in subjects hospitalised for COVID-19, compared to placebo
                       | 
 
Change from baseline (Day 1 pre-dose) in the viral load (RT-qPCR) of nasopharyngeal samples at Day 1, Day 3, Day 8 and day of discharge
 
                                                                                                                                                                                                                                                                                                                                                                                                                                                                                                                                                                                                                                                                                                                                                                   |

| PART 2 Objectives                                                                                                                                | PART 2 Endpoints                                                                                                                                                                                                                                                                                                                                                                                                                                                        |
|--------------------------------------------------------------------------------------------------------------------------------------------------|-------------------------------------------------------------------------------------------------------------------------------------------------------------------------------------------------------------------------------------------------------------------------------------------------------------------------------------------------------------------------------------------------------------------------------------------------------------------------|

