- **Endpoint assessment period (Day 2 to Day 29):** Subjects will remain hospitalised until at least 24 hours after study treatment administration. Hospital discharge after this period is at the discretion of the Investigator and will be based on the clinical condition of the subject. Study assessments will be performed every day up to Day 4 and then weekly until Day 29. Subjects who are discharged from the hospital before the Day 29 visit will return to the study site for each study visit until Day 29 (see Section 6.7 for details). Day 29 is considered as the EOS for part 1.
- **Extended follow-up period (Day 30 to Day 90) for part 2 only:** Subjects will return to the study site for 2 additional visits, on day 60 and day 90. Day 90 is considered as the EOS for part 2.

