### **9.4.1 General Considerations**

All statistical analyses will be performed by Parexel. All statistical analysis will be performed using the latest available version of SAS® (SAS Institute Inc., Cary, North Carolina, United States of America [USA]), version 9.2 or higher.

Continuous data will be summarised by treatment group using descriptive statistics (number, mean, median, standard deviation [SD], minimum, and maximum). Categorical data will be summarised by treatment group using frequency tables (frequency and percent).

Unless other way specified, baseline will be taken as the last available assessment prior to dosing on Day 1.

All statistical tests will be 2-sided and will be performed at the 5% level of significance, thus 95% confidence intervals (CIs) will be computed, unless otherwise stated.

A protocol deviation is defined as any change, divergence, or departure from the study design or procedures of a study protocol. Protocol deviations can lead to the exclusion of a subject from the PPS. Protocol deviations will be reviewed and classified at the Blinded Data Review Meeting (BDRM) prior to unblinding; the exclusion of subjects from PPS will be decided at BDRM.

Unless otherwise stated, missing data will not be imputed.

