### 9.4.3 Secondary Efficacy Endpoints

Proportion of subjects who are alive and do not require any form of mechanical ventilation at Day 8. Proportion of subjects requiring non-invasive or invasive, mechanical ventilation, proportion of subjects requiring intensive care unit (ICU) transfer, and all-cause mortality rate within 28-day FU period will be presented.

Total duration (days) of oxygen supplementation within 28-day FU period, change from baseline in the nasopharyngeal viral load (RT-qPCR) will be reported as continuous endpoints.

Proportion of subjects with clinical status evolving to each level of the 8-point ordinal scale at Days 2, 3, 4, 8, 15, 22, and Day 29, compared to baseline, will be tabulated in a shift table.

Time to event secondary endpoints will be analysed using a methodology similar to the analysis of the primary efficacy endpoint.

In Part 1, the secondary endpoints will be summarised descriptively.

In Part 2, the comparison between XVR011 and placebo will be conducted for every secondary endpoint and resulting p-values will be presented.

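### Two of the four time points in the Part 2 viral-load endpoint, Day 1 and day of discharge, cannot support a valid comparison between arms

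*Protocol*

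**What the plan says.** Table 3–2 (and the synopsis, in the same terms) gives one endpoint under the Part 2 antiviral objective: the change from the Day 1 pre-dose baseline "in the viral load (RT-qPCR) of nasopharyngeal samples at Day 1, Day 3, Day 8 and day of discharge". Section 9.4.1 sets the general rule that "baseline will be taken as the last available assessment prior to dosing on Day 1".

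In Table 1–2 the row "Viral load nasopharyngeal sample" has four entries: Day 1 marked pre-dose, Day 3, Day 8 and Discharge. There is no post-dose swab on Day 1, and none in the Day 90 or early-discontinuation columns. The discharge visit may fall on any day from Day 2 to before Day 90.

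Section 4.1 states what fixes that day: "Hospital discharge after this period is at the discretion of the Investigator and will be based on the clinical condition of the subject". The synopsis rationale gives the aim of treatment as to "achieve a more rapid recovery, reduction in the need for medical care", and time to sustained discharge is itself a secondary efficacy endpoint in Table 3–2.

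On analysis, Section 9.4.3 says that "change from baseline in the nasopharyngeal viral load (RT-qPCR) will be reported as continuous endpoints" and, for Part 2, that "the comparison between XVR011 and placebo will be conducted for every secondary endpoint and resulting p-values will be presented". It makes no allowance for when the discharge swab was taken. Part 1 secondary endpoints are descriptive only.

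**The concern.** A comparison of change from baseline is interpretable when both arms are measured at the same time after dosing and the measured subjects were not selected by the outcome. Day 1 and day of discharge each fail, in different ways.

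- **Day 1.** The value and its baseline are the same swab, so there is nothing to compare.
- **Day of discharge.** The sampling time is an outcome. If virus falls over the hospital stay and one arm goes home sooner, that arm is swabbed earlier in its decline and shows less fall. Subjects who die in hospital have no value. Section 8.1.1 also sends a subject who needs intensive care to the end-of-study visit, which has no viral swab, so some of the sickest subjects may never supply one.

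At stake is the reading of the only endpoint under the antiviral objective. The plan could give a discharge result that disagrees with Day 3 and Day 8 for reasons of timing alone, with no statement of which result carries the objective.

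**Working it through.** **Day 1.** Change at Day 1 = (Day 1 pre-dose swab) − (Day 1 pre-dose swab) = 0 for every subject in both arms. The variance is zero and there is no test.

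**Discharge: inputs.** The protocol states no effect size, variance or power for viral load, so there is no planned figure to reproduce. Table 9–1 gives the proportion not yet recovered at Days 5, 7 and 29: placebo 80%, 50%, 20%; XVR011 50%, 25%, 20%. I use recovery time as a proxy for discharge time. The rate of viral decline is not in the protocol and is my assumption.

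The curves can be checked against the table's own hazard ratios. The ratios of the piecewise hazards are (ln 2/4)/(ln 1.25/4) = 3.11, (ln 2/2)/(ln 1.6/2) = 1.475 and (ln 1.25/22)/(ln 2.5/22) = 0.24, against 3.11, 1.47 and 0.24 stated.

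**Formula.** Let s be the placebo decline in log10 per day, r the ratio of the XVR011 decline to the placebo decline, and T_x and T_p the days from dosing to discharge. Then

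XVR011 minus placebo at discharge = s × (T_p − r × T_x),

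where a positive value means less fall on XVR011. If both arms were swabbed at T_p the difference would be s × T_p × (1 − r). The shift caused by the date is therefore s × r × (T_p − T_x), which is positive whenever XVR011 subjects leave earlier.

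**Using medians.** Table 9–1 puts 50% at Day 5 for XVR011 and Day 7 for placebo, so T_x = 4 and T_p = 6 days after dosing.

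- Equal decline (r = 1): (6 − 4) × 0.2 = 0.4 and (6 − 4) × 0.5 = 1.0 log10.
- Difference of zero: r = 6/4 = 1.5. Above that it favours XVR011, though by less than it should.

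**Using means among those recovered by Day 29.** Within an interval of length w starting at time a, where the curve falls from S0 to S1, the mean time is a + w/ln(S0/S1) − w × S1/(S0 − S1).

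| Days after dosing | XVR011: share, mean | Placebo: share, mean |
|---|---|---|
| 0–4 | 0.50, 1.77 | 0.20, 1.93 |
| 4–6 | 0.25, 4.89 | 0.30, 4.92 |
| 6–28 | 0.05, 16.59 | 0.30, 15.34 |

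Weighting by share and dividing by 0.80 gives T_x = 3.67 and T_p = 8.08 days. With s = 0.3, Day 3 (2 days after dosing) and Day 8 (7 days) set beside discharge:

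| r | Day 3 | Day 8 | Discharge |
|---|---|---|---|
| 1.0 | 0 | 0 | 0.3 × (8.08 − 3.67) = +1.32 |
| 1.5 | −0.30 | −1.05 | 0.3 × (8.08 − 5.51) = +0.77 |
| 2.0 | −0.60 | −2.10 | 0.3 × (8.08 − 7.34) = +0.22 |

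For r = 1.5 with discharge at 8.08 days in both arms, the discharge difference would be 0.3 × 8.08 × (1 − 1.5) = −1.21. The change of sign comes from the date alone. On means the zero point is r = 8.08/3.67 = 2.2. Over s = 0.2 to 0.4 the discharge difference is +0.88 to +1.76 at r = 1 and +0.15 to +0.30 at r = 2. A simulation over the same slopes, with r from 1 to 2, an assumed detection floor of 2 log10 and an assumed baseline of mean 6.5 and SD 1.5, gave +0.16 to +1.12.

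**The case against.** **Scope.** A reader might infer that the whole antiviral comparison is biased against a drug that works, or that such a drug would look inactive on its only antiviral endpoint. The protocol does not support that. Day 3 and Day 8 are fixed days, and Section 6.7 brings discharged subjects back for scheduled visits, so the discharge date does not move those swabs. Nor does Day 1 bias anything. It is probably the swab schedule copied into the endpoint. In Part 1 there is no between-arm test to distort.

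**Left to the SAP.** Section 9.4.3 names no model and does not say that each time point is tested separately, and details are deferred to the SAP. That is fair as to the model, and the absence of baseline adjustment is no fault here. It does not dispose of the point: the protocol itself puts day of discharge inside the endpoint and promises a comparison with a p-value. An SAP that dropped it would depart from the protocol.

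**Size.** The 0.4–1.0 log10 figure describes a drug with no effect on viral decline. Faster clearance offsets part or all of it, and medians and means give different zero points (1.5 and 2.2). Recovery is also an imperfect proxy, since level 3 of the scale counts as recovered while still in hospital. These objections stand against any firm figure. They do not touch the direction of the shift.

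**Day 8 is not perfect either.** The intensive-care rule in Section 8.1.1 can also remove sick subjects before Day 8. That is a separate missing-data matter, which changing the time points does not cure.

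**Conclusion.** The point holds for two time points of one Part 2 secondary endpoint. Day 1 is an empty contrast. Day of discharge is a confounded and selected one, and it is shifted against XVR011 if viral load is falling and XVR011 brings discharge forward. The second condition is the trial's own hypothesis.

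The size is illustrative: 0.4–1.0 log10 on Table 9–1 medians, assuming an equal decline of 0.2–0.5 log10 per day in both arms and recovery as a stand-in for discharge. Whether the net result favours placebo, neither arm or XVR011 depends on how much XVR011 speeds clearance, which the protocol does not state. The primary endpoint and sample size are untouched, and Section 9.4.3 attaches no decision rule to viral load. The correction is worth making because it removes a misleading test from the antiviral objective at almost no cost.

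**What to change.** In the synopsis, Table 3–2 and Section 9.4.3:

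- Use the Day 1 pre-dose swab as baseline only and delete Day 1 from the list of change time points.
- Make the between-arm comparison of change from baseline at Day 3 and Day 8. Adjusting for baseline viral load is an optional gain in precision that needs no further data.
- Report the discharge swab descriptively, with its day of sampling and the number of subjects without one, and with no between-arm p-value.

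In the Part 1 endpoint list (synopsis and Table 3–1), which is descriptive, only the Day 1 wording needs correcting.

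The cost is wording. No sample or visit changes.

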## 4 Study Design

### 4.1 Overall Design

This is a 2-part Phase 1/2 clinical study to evaluate the efficacy and safety of XVR011 in subjects hospitalised for COVID-19.

**Part 1 (Phase I):** Part 1 consists of an open-label, single ascending dose, Phase 1 study to evaluate the safety of XVR011 administered as a single intravenous infusion, at 3 dose levels, and evaluate the PK, pharmacodynamic (PD), and initial efficacy of the treatment. Eligible subjects will be enrolled in 2 successive cohorts of 9 subjects, each. Two subjects in each cohort will be sentinel subjects monitored for at least 24 hours (first sentinel subject will be monitored for 24 hours before the second sentinel subject is treated and monitored for 24 hours) before the remaining subjects can be dosed and decision to open Cohort 2 will depend on the review of data collected from subjects enrolled in Cohort 1 after the last subject was treated and monitored for 24 hours. The same strategy will be followed for Cohort 3 (see Section 6.6.1 for details).

A phase 1a study (protocol EXEVIR0102) in healthy subjects is being conducted in parallel with Part 1 of this study. It is evaluating the same dose levels, namely 250, 500 and 1000 mg as a single IV infusion in a dose ascending design, with a placebo control. Per dose level, 8 subjects receive a single IV infusion of XVR011, and 2 subjects receive a single IV infusion of placebo in a blinded manner. The study will generate PK data and safety data not confounded by the disease state. An interim analysis of study EXEVIR0102 will be performed when all dose groups have received treatment and when the last dose group (1000 mg) has completed the 8-day follow-up. As discussed in section 4.3 Justification for Dose, the main driver for the dose determination is the target serum concentration and number of days this is exceeded, in addition to safety. The PK parameters from the healthy volunteers are considered predictive for the patient setting. The safety profile will be reviewed of the 3 different dose levels in the healthy subject study.

The IDMC will be asked to make a recommendation to progress to Part 2 (phase 2 design) of this study with the recommended dose based on the interim analysis of the Phase 1a study in 30 healthy subjects, supplemented with the available data from Part 1 of this study, even if not all Part 1 cohorts have reached the planned enrolment. This is due to recruitment challenges in Part 1 of this study resulting from low hospitalisation rate and reluctance of sites to participate and enrol patients in a phase I trial.

**Part 2 (Phase 2):** Part 2 consists of a double-blind, randomised, placebo-controlled Phase 2 study to evaluate the efficacy, safety, PK, and PD of XVR011 administered at the recommended dose level based on the IDMC review and recommendation. A total of 408 eligible subjects will be

randomised in a 2:1 ratio to receive either XVR011 (272 subjects) or placebo (136 subjects). Standard of care (SoC), according to local requirements will be allowed, except if listed in Table 6.5 Forbidden Concomitant Medications. Stratification will be done at randomisation for country and for fully vaccinated/prior SARS-CoV-2 infection. Subgroup analyses will include factors such as disease state, baseline serology, baseline viral load levels and duration of COVID-19 symptoms prior to study treatment.

For both Part 1 and Part 2 the study will consist of 3 periods: Screening (Day -1), Treatment period (Day 1), and Endpoint Assessment period (7 to 8 visits, Day 2 to Day 29); for Part 2 there will be an additional Follow-up period (2 visits, Day 60 and Day 90):

- **Screening (Day -1):** Subjects who are hospitalised and provide informed consent will undergo screening assessments as soon as possible after presentation with COVID-19 to evaluate their eligibility based on the inclusion and exclusion criteria. If eligible, the subject may be randomised (e.g for Part 1 this means IWRS treatment registration).
- **Treatment period (Day 1):** Within 12 hours of randomisation, a single intravenous infusion of study treatment will be started under medical supervision for the whole duration of the infusion and for two hours after the end of the infusion. This treatment will be administered in addition to SoC treatment.
- **Endpoint assessment period (Day 2 to Day 29):** Subjects will remain hospitalised until at least 24 hours after study treatment administration. Hospital discharge after this period is at the discretion of the Investigator and will be based on the clinical condition of the subject. Study assessments will be performed every day up to Day 4 and then weekly until Day 29. Subjects who are discharged from the hospital before the Day 29 visit will return to the study site for each study visit until Day 29 (see Section 6.7 for details). Day 29 is considered as the EOS for part 1.
- **Extended follow-up period (Day 30 to Day 90) for part 2 only:** Subjects will return to the study site for 2 additional visits, on day 60 and day 90. Day 90 is considered as the EOS for part 2.

## 4.2 Scientific Rationale for Study Design

This 2-part study consists of an open-label, single ascending dose, Phase 1 study to evaluate the safety, PK, PD and initial efficacy of XVR011 administered at 3 dose levels. Due to low rates of infection and hospitalisation at the Part 1 investigational sites and consequent recruitment challenges, a healthy subject Phase 1a study is being conducted in parallel which evaluates the

same 3 dose levels: 250 mg, 500 mg and 1000 mg. The safety and PK data from the healthy subject study, together with available data from Part 1 of this study will determine the recommended dose of XVR011, that will be used in a double-blind, randomised, placebo-controlled Phase 2 study to evaluate the efficacy, safety, and PK/PD of XVR011.

The dose-finding part of this first-in-human study (Part 1) follows the recommendations of the European Medicines Agency Guideline on strategies to identify and mitigate risks for first-in-human clinical trials with investigational medicinal products (EMA/CHMP/SWP/28367/07). Refer to Section 4.3 for the selection of the starting dose.

For Part 2, a double-blind, placebo-controlled design is appropriate and standard for an efficacy and safety study. This design will minimise bias and provide reference data (i.e., data from placebo-treated subjects), which will aid in the interpretation of results.

The primary efficacy endpoint for Part 2 is the time to sustained recovery within a 28-day follow up period, where recovery is defined based on an 8-point ordinal scale for COVID-19 clinical status used in previous studies involving subjects hospitalised for COVID-19 (Beigel et al 2020), and which is sustained for at least 14 consecutive days.

The proposed population is subjects, in whom the viral load is causing mild to moderate symptoms and who require supportive therapy such as hospitalised monitoring, treatment or supplemental oxygen but who are not in need of mechanical ventilation (i.e., level 4 or 5 of the 8-point ordinal scale). The aim of treatment with XVR011 is to neutralise the virus, to reduce the severity of the disease, and to prevent progression to severe complications such as ARDS or other major organ dysfunctions. Recovery is defined as reaching level 3 of the 8-point ordinal scale (i.e., subjects are hospitalised but no longer require supplemental oxygen or ongoing medical care for COVID-19) or less (subjects are no longer hospitalised for treatment of COVID-19). See also Section 2.1 and Section 2.2.

Study treatment will be administered in addition to SoC to limit the risk of disease progression for subjects randomised to placebo. For Part 2, concomitant use of remdesivir will be allowed as SoC, according to local guidelines.

Other small molecule antiviral agents such as molnupiravir and PF-07321332/ ritonavir may be continued at the discretion of the Investigator if they have been started prior to hospital admission for treatment of COVID-19 in accordance with their authorised use. However, they are not allowed if they are to be started once the subject is in hospital and in screening or already enrolled in the study.

Treatment with a SARS-CoV-2 neutralising monoclonal antibody for the current infection is not allowed with 4 weeks before and during the study, because of the similar mechanism of action and long half-life.

Stratification will be done at randomisation for country and for fully vaccinated/prior SARS-CoV-2 infection.

Subgroup analyses will include factors such as disease state, baseline serology, baseline viral load levels and duration of COVID-19 symptoms prior to study treatment.

Secondary endpoints to further evaluate efficacy include total duration of oxygen supplementation, proportion of subjects requiring mechanical ventilation or ICU transfer, subject-reported assessment of COVID-19-related symptoms following FDA Guidance for Industry (September 2020) and changes from baseline in viral load to evaluate antiviral activity.

Safety assessments will include standard adverse event reporting, physical examination, vital signs and ECGs, as well as the assessment of infusion related reactions (IRR) and hypersensitivity reaction.

